## Abstract

**Background:**

Chronic noncommunicable diseases such as arterial hypertension have a high impact in the context of public health. Previous studies have shown improvements in blood pressure due to simple lifestyle changes, which were supported by electronic health (eHealth) solutions.

**Objective:**

The aim of this study is to develop an eHealth platform and assess the effects of its use on the health conditions of patients with hypertension, with assistance from health professionals in the public health system of a Brazilian city.

**Methods:**

The platform will include a server that centralizes all the data and business rules, a website dashboard for health professionals, and a mobile app for patients. We will analyze the effects of its use through a controlled, nonrandomized, nonblind, prospective, monocentric clinical trial. We will enroll 68 participants diagnosed with arterial hypertension and under medical follow-up and categorize them into two groups. The participants of the intervention group will use the platform as a monitoring method, whereas the participants of the control group will use conventional methods. In both groups, we will assess and compare the evolution of blood pressure and treatment adherence before, during, and after the intervention.

**Results:**

The project was funded at the end of 2018. We have been developing the software since 2019 with plans to complete it in 2020, and we will enroll patients between 2020 and 2021. We expect to submit the first results for publication in 2020.

**Conclusions:**

For the primary outcome, we expect a reduction and stabilization of blood pressure. For the secondary outcomes, we hope to see improvements in treatment adherence, physical activities and dietary practices, and acceptance of the eHealth platform. In public health, the technology that favors disease control also helps reduce complications and, consequently, treatment costs. The platform might encourage the adaptation of medical assistance to incorporate this technology into patient monitoring.

**International Registered Report Identifier (IRRID):**

PRR1-10.2196/15299

## Introduction

### Background

Chronic noncommunicable diseases such as arterial hypertension are responsible for a high frequency of hospitalizations and have a great socioeconomic impact [1]. In Brazil, the direct and indirect costs of these diseases have been increasing significantly [2]. Currently, 32% of the Brazilian adult population, which corresponds to 36 million individuals, has hypertension [3]. However, only about half of the patients under treatment for hypertension report that their blood pressure is within the recommended levels [3,4]. As hypertension is a chronic condition, the best approaches for a healthy life are the awareness, treatment, and management of the disease.

With this perspective, the Brazilian Ministry of Health developed a system called Brazilian Clinical Management System of Arterial Hypertension and Diabetes Mellitus (SIS-Hiperdia) for registering and monitoring patients with arterial hypertension and diabetes mellitus, with assistance from the health professionals in the outpatient clinics of the Brazilian public health network. However, patients’ data are required for continued working of this system, and it is not feasible to obtain this information if patients do not have a history of their health conditions available [5]. Moreover, a strategy developed for use only in clinical centers may not be enough to treat the disease and change habits. Developing and using complementary tools is necessary for both physicians and patients [6]. Therefore, the electronic health (eHealth) systems have been attracting an increasing number of users because of the diffusion of mobile devices and the growing interest in better quality of life and health care [7]. The World Health Organization [8] announced that eHealth solutions might transform the resources of health services worldwide. Most regions in the world, including low- and medium-income countries, are working actively on eHealth projects [8], including Brazil.

Previous studies have shown positive results in the improvement of blood pressure from simple lifestyle changes supported by eHealth solutions [9]. The results by Toro-Ramos et al [10] indicated a decrease in diastolic pressure and body weight of the 73 participants. In the study by Ashoorkhani et al [11], tests for 132 patients with hypertension showed an improvement in treatment adherence, weight control, and regular blood pressure verification. The study by Albini et al [12] with 690 hypertensive patients suggests that information and communication technology tools may be effective in providing physicians with dynamic patient control and in improving the monitoring of hypertension and adherence to treatment prescriptions.

In the studies mentioned above [10-12], periodic verification was essential for obtaining favorable results. However, a prominent challenge in the market of mobile apps is maintaining long-term or recurrent use of the app among users engaged with the app, without loss of interest. Among the leading causes of abandonment from the users of these apps are quitting after achieving goals and the lack of resources available [13]. Several techniques have been used to allow greater user engagement with the app, such as gamification, which comprises applying gaming elements to a nongaming context [14].

### Prior Work

We have devised a platform for monitoring the health conditions of patients with arterial hypertension. We implemented an initial version, considered a prototype, and made it available to use for initial validations. The platform includes a server that centralizes the data for a website interface [15] that is designed for health professionals, and a mobile app with gamification elements [16] that is designed for patients.

We performed pilot studies with health professionals and patients to assess the prototype functionalities [15] and patient engagement and experience with the app [16-18], respectively. The assessment with health professionals showed some benefits of using the system, such as the optimal visualization of patients’ logbooks. Patient assessments showed that gamification favors engagement with health treatment. We also found that participants under follow-up with a health professional interacted more with the app and were more motivated to maintain their health monitoring. Therefore, the use of digital health resources by professionals, along with patients, may promote a higher commitment to monitoring the treatment factors [17]. To verify the clinical effects, we have already conducted a pilot trial [19], including 39 patients with arterial hypertension, to compare the use of the platform’s initial version with conventional hypertension monitoring over a period of 3 months. The patients who used the mobile health app had a change in systolic and diastolic pressure toward more adequate levels. In addition, the group had improved levels of glucose and high-density lipoprotein cholesterol and a reduced consumption of ultraprocessed foods.

The main goal of our project is to assess the effects of using the eHealth platform—which will be developed—on health conditions of patients with hypertension, with assistance from health professionals in the public health system.

## Methods

### Notice MS-SCTIE-Decit CNPq 12/2018: Research on Health Innovation

Our eHealth platform potentially favors the public health system by allowing the monitoring of health conditions of patients with hypertension, assessing risk, and supporting behavior changes. However, as it is an initial version, the software still requires improvement and the development of other functionalities and resources. The new characteristics predicted include a nutritional assessment model, a recommendation system, and the integration with wearable devices equipped with physiological sensors to automate data collection.

After a strict selection process of Notice MS-SCTIE-Decit CNPq 12/2018, the Brazilian Ministry of Health and the Brazilian Counsel of Technological and Scientific Development granted our project with research funding. Considering the potential for health innovation, they selected our eHealth platform for full development and testing in the Brazilian public health system.

**Figure 1 figure1:**
[figure not shown]
Computing architecture of the electronic health platform.

#### Website Dashboard

We designed the dashboard for health professionals, so that they could follow-up and monitor patients in real time. The professionals have access to patient information, and they may assess risks and advise patients remotely. In addition, the dashboard has an interface for the administrator to control business rules and data processing, with settings related to the frequency of alerts, monitoring the schedule of patient reminders, user access control, clinical guide parameters (eg, blood pressure, body fat, and body mass index), and messaging, among others.

After registration and access, the system forwards the professional to the functionalities of messages and alerts on patient measurements. To start the monitoring of a patient, professionals need to link the patient profile to their account. After patient authorization, the professional will have access to the patient’s logbook of blood pressure, heartbeat, weight, mood, waist circumference, body fat, sleep, physical activity, schedule, and dietary intake assessment. The platform can display all the data in graphic, interactive, and associated views.

More than one health professional may assist the patient, for instance, a cardiologist, a dietitian, and a psychologist. Thus, each professional may choose the information they wish to supervise according to each patient and the patient’s specific treatment. When selecting an item, the professionals proceed to a screen containing detailed information of the patient’s history to select what period they want to visualize. They may also view the reminders included by the patient, enter new reminders, and communicate with the patient through a private chat.

The study by Veiga [15] presented all the details of the functional prototype. The dashboard prototype will be the basis for the full development of the new version, which will also include new functionalities such as modules for nutritional assessment and recommendation of physical exercises and dietary habits for each patient profile, as developed by Ferreto [20].

#### Mobile App

The app allows users to record their data, send and receive notifications, communicate with their medical team, and pair the wearable device that will be developed. After installation and first registration, the patient can access the main interface containing his or her last measurements. Through the main interface, users can access the menu with the list of functionalities available, which include height, physical activity, heartbeat, waist, body fat, mood, weight, blood pressure, sleep, reminders, and chat. In the new version, other records will be available, including dietary intake and improvement of physical activity data. When selecting a functionality, patients can view their record information and graphs, and they may include, change, or delete data.

For the measurements, the patient records the date, time, value, and an optional observation. All operations with patient data synchronize with the central server. Periodically, the app displays alert notifications and reminders on the health data recorded, including notes sent by the health professional. Each notification presents a title, a brief description, and buttons with *yes* and *no* options. When clicking *yes*, the system sends the information to the server, showing whether the patient completed the action or reminder presented, for instance, whether they took the medication or visualized the message from the health professional. Such integration aims at continuous monitoring and the stimulus to maintain healthy practices.

We designed all functionalities of the app to engage patients with a regular health follow-up. In addition to the gamification elements, they also receive reminders and notifications on their health and interact with health professionals. The app has a functionality responsible for notifying the patient and the professional about health evolution through counseling based on clinical guidelines. At each insertion of patient data, the system analyzes the information according to the guidelines and issues an alert notification if the measurement is identified as different from the standard patterns. On the basis of these notifications, the patient may analyze and decide what to do next, including using the messaging functionality to contact the health professional for assistance. This integration does not replace personal visits, but it provides both the patient and professional with a fast and accessible communication tool for doubt resolution and guidance. All the records create a lifestyle logbook of the patient under monitoring, which may represent a source of information for the decision-making process of professionals.

The study by Cechetti et al [17] presented all the details of the functional prototype. The app prototype will be the basis for the full development of the new version, which will also include new functionalities corresponding to the ones predicted for the website dashboard.

#### Wearable Sensor Device

We will build a device equipped with modules of physiological sensors available in the market, such as oximeter and pedometer, compatible with the LilyPad Arduino—a mini-controller board designed for wearables and intelligent textiles. The device will have a communication routine with the mobile app through the Bluetooth protocol to automate the measurement records.

First, we will assess the use of the wearable device in a group of 10 individuals. We will connect the device to a piece of clothing (eg, T-shirt, wristband, and glove) worn by the participant to monitor the physiological signs during daily activities such as walking, lying down, and nonexhaustive work. On the basis of a study by Zhou et al [21], we prepared a questionnaire to assess the level of comfort while using the device. If we detect any nuisance in the comfort assessment, we will adjust the device to suppress such discomfort.

We will perform technical trials to test the correct functioning of the equipment and wireless communication assessments with performance measures (eg, response time, package traffic, and latency) and the request acknowledgment and checksum. We will also evaluate the behavior of electronic components attached to the hardware modules to ensure the reliability and accuracy of the collected data. For this validation, we will compare values obtained by the sensors with values recorded by reliable conventional devices used by health professionals, such as sphygmomanometer, heart monitor, and pulse oximeter. We will perform all assessments of the wearable sensor device separately in substudies, which will not be a part of the main clinical trial.

### Nonrandomized Controlled Trial

This is an applied research of technological innovation with software development and analysis of its effects through a controlled, nonrandomized, nonblind, prospective, and monocentric clinical trial. The Research Ethics Committee of the University of Passo Fundo, Rio Grande do Sul, Brazil (report 3.414.793) approved this project, which was registered in the Brazilian Platform of Clinical Trials under the code RBR-2rkkgn (Universal Trial Number U1111-1230-7550). Figure 2 presents the trial design and flowchart.

**Figure 2 figure2:**
[figure not shown]
Trial procedure flowchart. eHealth: electronic health; MBG: Martín-Bayarre-Grau; SUS: System Usability Scale; TAM: technology acceptance model.

#### Study Population and Sample

The study population will include men and women under treatment for arterial hypertension who will be assisted by health professionals in the public health system of a Brazilian city. After the invitation to take part in the study, the participants will sign a consent form. The effect (primary outcome) is expected to be 80% in the intervention group and 40% in the control group, which means a 40% difference. These proportions are based on the findings of the study by Neumann et al [22], which was conducted with a similar design, and also on more optimistic results obtained from one of our pilots [19]. For sample calculation, we used Epi Info version 6.0 software (Centers for Disease Control and Prevention, Atlanta, Georgia; sample size/2 proportions). We considered an estimate of 40% proportion difference between groups, 95% confidence interval, and 80% statistical power (beta). The calculation resulted in 28 individuals for each group, but to minimize the effects of loss and refusal during the intervention, we added 20% to the size, yielding a total of 34 individuals in each group.

The allocation of patients in each group will be based on the eligibility criteria. For example, if the patient fits all the criteria but does not have a mobile phone compatible with the app, then he or she will be allocated to the control group. If the patient has a mobile phone compatible with the app, he or she will be allocated to the intervention group. For propensity score calculation, based on the effect of confounding factors or predictors of exposure (to intervention), we will consider demographic variables of age, gender, and socioeconomic status.

We will consider the following inclusion criteria:

Cognitive ability confirmed by the Mini-Mental State Examination [23] (both groups)Current medical monitoring for the treatment of hypertension in the public health system of the city of Passo Fundo, RS, Brazil (both groups)Possibility to measure blood pressure in drugstores, hospitals, Family Health Strategies, or centers for comprehensive health care (both groups)Possession of an Android mobile phone, version 4.3 or higher (intervention group)Familiarity with the use of apps (intervention group)Internet access on the smartphone (intervention group).

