#### Statistical and Qualitative Analysis

Our expectation for the primary outcome is the reduction and stabilization of blood pressure. For the secondary outcome, we hope for acceptance of the eHealth platform and improvements in treatment adherence, physical activities, and dietary intake. A priori levels will be set according to the assessment tool and the expected outcome. The acceptance of the eHealth platform will consider good scores obtained in the analysis of usage logs and questionnaires of engagement, SUS, and TAM. Improved adherence to treatment will consider MBG questionnaire scores measured before and after the intervention. For the analysis of physical activities and dietary intake, a binary outcome will consider whether the patient has adequate levels, diagnosed according to the SISVAN’s questionnaire and standards.

For qualitative data, we will use Minayo’s guidelines [30]. Numeric data will be analyzed with statistical software SPSS 22 (IBM Corp, Armonk, New York). We will calculate the measures of central tendency and dispersion of the quantitative variables, and we will use the Kolmogorov-Smirnov test to verify normality. Basic quantitative data will be determined by mean, standard deviation, and median. Categorical data will be determined by simple frequency. Blood pressure data will be analyzed with the paired *t* test. Either the paired *t* test (parametric) or the Wilcoxon test (nonparametric) may be applied to compare other quantitative variables before and after the intervention. To assess treatment adherence, physical activity, and dietary intake after intervention, we will apply the Chi-square test while considering the app use as the dependent variable; the independent variables will be treatment adherence, physical activity, and dietary intake. For the MBG questionnaire, we will apply the Mann-Whitney test to compare the score between the groups before and after the intervention. The same test may be used to compare diastolic and systolic blood pressure measurements between the preintervention and postintervention groups. We will consider a 95% confidence interval (*P*<.05).

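### The stated 80% power is for a between-group comparison of blood pressure proportions that no listed analysis makes; the only committed blood pressure test is within-group

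*Protocol article*

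**What the plan says.** The protocol article, Study Population and Sample, states that the primary outcome "is expected to be 80% in the intervention group and 40% in the control group", a difference of 40 percentage points. It attributes these proportions to a cited study of similar design and to more favourable results from one of the group's own pilots. The calculation used the two-proportions routine of Epi Info 6.0 with 95% confidence and 80% power. "The calculation resulted in 28 individuals for each group", and then "we added 20% to the size, yielding a total of 34 individuals in each group".

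Statistical and Qualitative Analysis describes the outcome differently: "Our expectation for the primary outcome is the reduction and stabilization of blood pressure". It gives no rule for when a patient counts as having met this. The tests it lists are:

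- **Blood pressure, committed:** paired t test.
- **Blood pressure, optional:** a Mann-Whitney test may be used on systolic and diastolic measurements. The sentence speaks of preintervention and postintervention groups, so it is not even certain that the study arms are meant.
- **Chi-square on proportions:** adherence, physical activity and diet only.
- **Chi-square at P<.10 with I²:** a heterogeneity check.
- **Logistic regression, if feasible:** app use is the dependent variable; the predictors named are sociodemographic variables and secondary outcomes.

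**The concern.** The powered comparison and the listed tests differ in two ways. First, the sample size treats the primary outcome as an event that each patient has or does not have, while the analysis treats blood pressure as a measurement. Second, the sample size compares the intervention group with the control group, while the committed test compares each group with its own baseline.

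The second difference matters more. A paired t test can be significant in the app group because of regression to the mean, closer attention during a study, or a change of medication over three months. A significant change in one group and a non-significant change in the other is not evidence that the groups differ. If the results are reported as listed, the control group contributes nothing formal to the primary conclusion, and the quoted 80% power says nothing about the test actually reported.

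**Working it through.** **Inputs.** From Study Population and Sample: p1 = 0.80, p2 = 0.40, power 0.80, equal groups. Two-sided alpha of 0.05 is assumed from the 95% confidence level.

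**1. Reproducing 28 and 34.**

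Uncorrected size: n′ = [z(0.975)·√(2p̄q̄) + z(0.80)·√(p1q1 + p2q2)]² / d², with p̄ = 0.60 and d = 0.40.

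- 1.960 × √0.48 = 1.358
- 0.842 × √(0.16 + 0.24) = 0.532
- n′ = (1.358 + 0.532)² / 0.16 = 22.3, so 23

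With continuity correction: n = (n′/4)·[1 + √(1 + 4/(n′d))]² = 27.1, so **28**, which matches. One-sided versions give 18 without and 23 with correction, so the powered test is identified without ambiguity. The allowance also matches: 28 × 1.2 = 33.6, so **34**.

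Power at 28 per group is 81.6% corrected and 88.5% uncorrected.

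**2. Looking for that test among the listed analyses.**

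| Listed analysis | Blood pressure? | Proportion? | Between groups? |
|---|---|---|---|
| Paired t test (committed) | yes | no | no |
| Mann-Whitney (optional) | yes | no | possibly |
| Chi-square | no | yes | yes |
| Logistic regression (if feasible) | not named | no | app use is the dependent variable |

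No row has yes in all three columns. For physical activity and diet the same section does state a binary outcome, so the authors specify one where they intend it.

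**3. What 28 per group gives for measured pressure.** For an unadjusted two-sample t test at 80% power the detectable difference is 0.76 SD (normal approximation: (1.960 + 0.842) × √(2/28) = 0.75). Adjusting for baseline multiplies it by √(1 − r²). The article gives no correlation, so r is an assumption:

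| r | √(1 − r²) | Detectable difference (SD) |
|---|---|---|
| 0.5 | 0.866 | 0.66 |
| 0.6 | 0.800 | 0.61 |
| 0.7 | 0.714 | 0.54 |

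**4. Is 0.76 SD a shortfall against the planned effect?** Assume normal values, equal variances and a common cut-off. Then 80% versus 40% corresponds to 0.842 + 0.253 = 1.095 SD. At 28 per group the power for that shift is about 98% by t test and 97% by Mann-Whitney (simulated). It is not a shortfall.

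**5. Conditional sensitivity.** This applies only if the binary outcome means pressure at target. Take a control rate of 50% and hold the intervention rate at 80%. For the corrected test replace n by n(1 − 1/(nd))²; at n = 28 and d = 0.30 this is 28 × (1 − 1/8.4)² = 21.7. Then z = (0.30 × √21.7 − 1.322)/0.640 = 0.12, giving 54.7%.

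| Evaluable per group | Corrected | Uncorrected |
|---|---|---|
| 28 | 54.7% | 66.1% |
| 34 | 65.5% | 74.8% |

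Reaching 80% power would take 45 per group corrected or 39 uncorrected. If the 40-point gap is kept instead (90% versus 50%), 28 per group gives 87.0% corrected.

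**The case against.** Three arguments can be made for the plan.

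**The detail may sit in an analysis plan not shown, and the article allows techniques to be adjusted.** A full model specification may well be elsewhere. But this article names a blood pressure test and also quotes a power, and the two do not belong together. A clause allowing modification does not supply the missing comparison; it leaves the choice open until the data are seen. The propensity score mentioned under Study Population and Sample is not tied to any blood pressure comparison either.

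**The sample may be ample.** This stands. Measured pressure carries more information than a yes/no version of it, and under the assumptions in step 4 a between-group test has well over 80% power for the planned effect. The defect is that the power statement is detached from the analysis, not that 68 patients are shown to be too few.

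**The 40% control rate has its own stated sources.** This also stands. The Background says that "only about half of the patients under treatment for hypertension report that their blood pressure is within the recommended levels", and entry requires treatment but no blood pressure threshold. A reader might infer that the document itself implies a 50% control rate and hence about 55% power. It does not. The Background figure is national and self-reported, the 40% is attributed to a cited study and the pilot, and an undefined responder could equally be a patient whose pressure fell. The 55% is also the lowest of the standard choices.

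**Conclusion.** The point holds as a mismatch between the powered endpoint and the listed analysis. The arithmetic of 28 and 34 is correct, but the 80% power belongs to a test the article does not list for blood pressure, and the one test it commits to does not compare the groups. This rests on the article's text alone.

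The sensitivity to a 50% control rate is conditional: about 55% to 66% power at 28 per group and 66% to 75% at 34 (corrected to uncorrected). It needs the outcome to be pressure at target and the intervention rate to stay at 80%. The detectable differences for measured pressure rest on the assumed correlations and on equal groups, and allow nothing for adjusting for confounders in this nonrandomized design.

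One minor note: adding 20% to 28 is done correctly as described. If 20% of the 34 were lost, 34 × 0.8 = 27.2 would remain (28/0.8 = 35). That is a difference of convention, not a defect.

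**What to change.** Keep 68 patients. Before the analysis, name one between-group primary blood pressure analysis at 3 months and rewrite the power sentence for it. Either of the following would do:

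- **Measured outcome.** Compare systolic pressure between groups, adjusted for baseline. State that 28 evaluable patients per group give 80% power for about 0.54 to 0.66 SD at assumed correlations of 0.7 to 0.5, and 0.76 SD unadjusted. Keep the paired t tests as descriptive.
- **Binary outcome.** Define the event behind the 80% and 40% and test it between groups. The present 28 then stands for those rates. If the event is pressure at target, add the power at a 50% control rate from the table above.

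The measured outcome makes better use of a sample of this size. The binary outcome stays closest to the existing calculation, but it exposes the trial to low power if control-group rates exceed 40%. Either way the cost is text only, with no extra patients or visits. The stated power may become less favourable, but it will belong to the test that is reported.
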